### **5.5 Blinding Arrangements**

Participants will be blinded to group allocation by the process of limited disclosure (see above). Participants will not be informed about the study hypotheses, or which group they were allocated to, until the study is completed, at which time they will be provided a lay summary of study purpose, hypotheses and findings. As the primary outcomes are participant-reported, and participants are blinded, the primary outcomes are considered assessor-blinded. Secondary outcomes consist of both participant-reported and objective measures which will also be considered outcome assessor blinded. Research staff entering the data will be blinded. Statistical analyses will be performed blinded. Descriptive baseline characteristics that are researcher-measured using objective methods in the laboratory (e.g. height, weight, physical function performance, muscle strength, cardiorespiratory fitness and body composition) will be measured by a blinded researcher. Physiotherapists will also be unblinded to the study hypotheses.

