|-------------------------------------------------------------------------------------------------------|----------------------------------------------------------------------------------------------------------------------------------------------------------------------------------------------------------------------------|----------------------------------------------------------------------------------------------------------------------------------------------------------------------------------------------------------------------------------|---------------------------------|
|                                                                                                       | indicate the frequency of use (over the past 6 months) of a range of pain and arthritis medications and co-interventions.                                                                                                  | drug/supplement at least once a week in the past month will be reported as a current user of the relevant medication. Participants who have used a co-intervention once in the past 6 months will be reported as a current user. |                                 |
| Adverse events                                                                                        | Recorded by participants using a custom-developed table.                                                                                                                                                                   | Proportions of participants experiencing adverse events will be reported.                                                                                                                                                        | 3 months and 9 months           |
| Expectation of treatment outcome                                                                      | Rated using a Likert scale with anchors of “no effect at all” to “complete recovery”                                                                                                                                       | The number and proportion of participants selecting each response option will be reported.                                                                                                                                       | Baseline                        |

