### 5.3 Informed Consent Process

The Chief Investigator will ensure that the Trial Coordinator is trained in obtaining informed consent for this research. All potential participants will receive verbal and written information about the purposes, potential risks and processes involved in the study from the Trial Coordinator. In accordance with the latest revision of the World Medical Association Declaration of Helsinki, informed consent will be obtained from all participants by signing a consent form after the researcher is certain that the participant understands the information delivered and has had an opportunity to ask questions and before proceeding with the baseline assessments.

Volunteers will initially be screened by an online form, then a subsequent telephone screening will involve a detailed verbal description of the project to ensure that participants are comfortable with and able to comply with trial procedures and have had the opportunity to have all questions answered. Participants deemed eligible at this stage will be sent the Plain Language Statement (PLS) and Consent Form in the post or by email (via REDCap).

Participants will be encouraged to phone researchers if they have any questions or concerns regarding the contents of the PLS and/or Consent Form. After reading the PLS, and if they give their consent to participate, they will sign the consent form online via REDCap or return it via a reply-paid envelope in the post or by scanning and emailing the document to the Trial Coordinator.

To ensure participant blinding (see below), the PLS and consent processes will involve limited disclosure about the specific exercise programs under investigation and study hypotheses. Participants will be informed that the trial is evaluating two different undisclosed “types” of exercise to compare effects on hip OA symptoms. Participants will not be told about the specific characteristics of the exercise under investigation.

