## 8. INTERVENTION

This 9-month study includes 3-month exercise programs delivered by a physiotherapist followed by a continuation of the exercise program independently for a further 6 months. Participants in both groups will attend 9 online treatment sessions via Zoom, over the first 3 months. Once per week over the first 6 weeks and fortnightly thereafter. The first session will be up to one hour with subsequent sessions up to 30 minutes. Physiotherapists will provide participants with home-based strengthening exercises in paper format, containing exercise instructions. Participants in both groups will be prescribed exercise dosage (i.e. frequency, intensity, time) according to the American College of Sports Medicine (ACSM) recommendations. A 2017 meta-analysis in this area demonstrated that exercise programs prescribed in accordance with ACSM dosage recommendations resulted in greater symptom improvement compared to exercise programs with questionable concordance to ACSM dosage recommendations. Feasibility and acceptability of aerobic and strengthening exercise prescribed according to ACSM dosage recommendations has been demonstrated in our recent pilot study (HREC. 1851762). Participants will be provided with an ankle-cuff weight and resistance bands. Participants will also receive a wearable activity monitor to wear daily for the initial 3 months of the study.

**Strengthening only:** Participants will be instructed by the physiotherapist how to perform 5-6 lower limb strengthening exercises, including how to use equipment such as ankle cuff weights and exercise resistance bands. Initial sessions will involve 1 to 2 sets of 8 to 12 repetitions at an intensity deemed by the participant to be at least 'hard' ( $\leq 7$ ) on the modified Borg Scale of rating of perceived exertion (RPE). The dosage will increase as appropriate to 3 sets at 'hard to very hard' (between 7 to 8) on modified RPE Borg Scale (*Modified Borg Scale; 10 is maximal effort*). Strengthening exercises will take approximately 30 minutes per session. Participants will be asked to complete these three times per week at home.

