**Aerobic & strengthening:** Participants will be prescribed muscle strengthening exercise as above. They will also be facilitated to build up to engaging in 150 minutes of moderate intensity aerobic exercise per week, which will be tailored to individual preferences, including a choice of activities such as walking, cycling and swimming. Participants will be encouraged to incorporate exercise into their daily lives and guided to gradually increase their aerobic activity to a moderate intensity of 30 minutes, 5 days a week with blocks of at least 10 minutes being appropriate. Physiotherapists will guide participants to self-monitor their aerobic exercise at a moderate intensity equivalent to at least 'somewhat hard' on the Borg RPE Scale (13-14) and corresponding heart rate, monitored on a wearable heart-rate sensor.

Following 3 months of guided exercise by the physiotherapists, participants will be encouraged to maintain the exercise program over the subsequent 6 months unguided.

**Physiotherapists:** We will recruit approximately 8 practising musculoskeletal physiotherapists in metropolitan Melbourne to deliver interventions for the trial on Independent Contractor Agreements. The same therapists will deliver intervention to both groups online via Zoom. The intervention will be protocolised. Participants will be randomly allocated to a physiotherapist.

To be eligible to deliver the intervention in this clinical trial, physiotherapists must:

- hold current registration to practice as a physiotherapist;
- have a receptionist at their clinical practice to facilitate patient booking and communication with research staff;
- have an Australian Business Number;
- be willing to undertake trial training requirements (see below);
- be willing and able to deliver interventions between July 2019 and Sept 2022;
- practice around the metropolitan Melbourne area;
- have treated at least five individuals with hip OA in the past 12 months.

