**Physiotherapist training**

Physiotherapists will be required to attend the University of Melbourne for a 4-hour training session. The training will address clinical trial procedures and treatments. Treatment manuals and copies of patient resources (e.g. exercise sheets and information brochures for handouts) will be provided to the physiotherapists in electronic and hard-copy. Physiotherapists will be provided with a Zoom Information Booklet that contains detailed step-by-step instructions on using Zoom. Physiotherapists will also receive personal assistance from the Trial Coordinator to ensure they are comfortable using the technology prior to their first online consult.

**Treatment fidelity:** Paper-based treatment notes from each consultation will be assessed by research staff for physiotherapist adherence to trial protocols. Fidelity will be recorded as the number and proportion of consultations where the RPE equalled or exceeded 'some-what hard' for aerobic component (i.e. 13-14 on the Borg RPE scale) and 'very hard' for the strengthening program (i.e. 7-8 on the modified Borg scale). The mean (SD) rating of perceived exertion for each participant's exercise program will be determined over their consultations, as recorded in the treatment notes.

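### Section 5.5, as written, has the therapists who treat both arms aware of the hypotheses that participants must not learn, with no non-disclosure safeguard stated; the sentence needs correcting or confirming

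*Protocol*

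**What the plan says.** The arrangement for participants is set out in two places. Section 5.3 says that "the PLS and consent processes will involve limited disclosure about the specific exercise programs under investigation and study hypotheses". Section 5.5 adds that "Participants will not be informed about the study hypotheses, or which group they were allocated to, until the study is completed". Participants know that two types of exercise are being compared, but not what characterises either.

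Both primary outcomes, the pain rating and WOMAC physical function, are completed by the participant (section 4.6). Section 5.5 derives their blinded status from that of the participant: "As the primary outcomes are participant-reported, and participants are blinded, the primary outcomes are considered assessor-blinded".

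Section 5.5 then goes through data entry, statistical analysis and laboratory measurement, all blinded, and ends with "Physiotherapists will also be unblinded to the study hypotheses".

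On delivery, section 8 states "Participants in both groups will attend 9 online treatment sessions via Zoom, over the first 3 months" and, of the approximately eight physiotherapists, "The same therapists will deliver intervention to both groups online via Zoom". On preparation it says "The training will address clinical trial procedures and treatments". It also calls the intervention protocolised and has fidelity recorded as perceived-exertion levels taken from treatment notes.

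**The concern.** Participants can see what exercise they do, so their blinding cannot be to the content of their own programme. It consists of not knowing the alternative or which programme is expected to do better. The primary objective (section 3.1) is directional: the combined programme is expected to reduce pain and improve function more.

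Therapists must know which programme they deliver, but they do not need to know which one is expected to win. A therapist who does know can convey more confidence to one arm than to the other, without intending to. Self-rated pain and function are open to that influence, and it would act in the direction of the hypothesis. At stake is the claim that the trial is participant- and assessor-blinded for both primary outcomes.

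**Working it through.** **1. The chain of dependence.** Section 5.5 makes assessor blinding of the primary outcomes follow from participant blinding. Sections 5.3 and 5.5 make participant blinding follow from limited disclosure. Read literally, the last sentence of 5.5 gives the undisclosed information to the people in repeated contact with participants.

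**2. Contact before the endpoint.** Section 8 gives nine sessions: weekly for six weeks, then fortnightly. The first is up to 60 minutes and the rest up to 30, so at most 60 + 8 × 30 = 300 minutes, or 5 hours. This is a maximum and is the same in both arms. It shows opportunity, not differential exposure.

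**3. Safeguards stated.** None addresses this route directly. The description of training does not mention withholding the hypotheses. The recorded fidelity measures concern exertion. Stratification by therapist (section 5.4) and the therapist random effect (section 10.3) deal with differences between therapists, whereas this bias would lie between arms within each therapist. "Expectation of treatment outcome" (section 4.6) is collected at baseline only, and section 5.4 reveals allocation after the baseline outcomes, so it cannot show expectations diverging between arms.

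**4. The plan's own sample size.** Inputs from section 10.1: SD 2.2 (pain) and 13 (function); baseline to follow-up correlation 0.46 and 0.40; target differences 1.8 and 6; 90% power; 5% significance, taken here as two-sided.

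- Baseline-adjusted SD = SD × √(1 − ρ²). Function: 13 × √(1 − 0.40²) = 11.91. Pain: 2.2 × √(1 − 0.46²) = 1.953.
- n per group = 2 × (1.960 + 1.282)² × (adjusted SD)² / Δ². Function gives 83 and pain gives 25.
- Allowing for 15% loss: 83 / 0.85 = 97.6, so 98 per arm and 196 in total.

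The stated figures reproduce, and function drives them.

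**5. What a reporting shift would do.** SE = adjusted SD × √(2/83): 0.303 for pain and 1.85 for function. With no true effect and a shift b favouring the combined arm, the chance of a significant result in its favour is 1 − Φ(1.96 − b/SE). At b = 0 this is 2.5%.

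| Outcome | Assumed shift b | Share of target | b/SE | False significant result favouring combined arm |
|---|---|---|---|---|
| Pain | 0.25 | 14% | 0.82 | 12.8% |
| Pain | 0.50 | 28% | 1.65 | 37.8% |
| Pain | 0.75 | 42% | 2.47 | 69.6% |
| Function | 1 | 17% | 0.54 | 7.8% |
| Function | 2 | 33% | 1.08 | 19.0% |
| Function | 3 | 50% | 1.62 | 36.8% |

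The shifts are assumptions; the protocol gives no figure for them. Pain is the more exposed outcome because a trial sized for function is large for pain.

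**The case against.** *The sentence may be a slip.* Every party listed before it is blinded, so 'also' fits 'blinded' well. It could equally mean unblinded to the hypotheses in addition to allocation. No other section settles it. This stands, and it limits the point to what the text says as written. It does not remove the need to act, because the sentence has to be corrected in one case and the practice changed in the other.

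*A reader might infer that therapists are briefed on the hypotheses.* The text does not show this. It says unblinded, and the training description does not mention hypotheses.

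*A reader might count treatment of both arms by the same therapists as a fault.* It is not. It keeps therapist from being confounded with arm. It matters here only because a therapist who knows the hypothesis meets participants from both sides of it.

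*Therapists will guess anyway.* Both arms get the same strengthening programme and one gets aerobic exercise in addition, so the question is easy to infer. This largely stands and limits what withholding the hypotheses can achieve. A non-disclosure instruction still works for a therapist who has guessed.

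*Other measures could reveal a difference.* The Working Alliance Inventory at 6 weeks and satisfaction at 6 weeks and 3 months (section 4.6) come after allocation and could pick up differences in therapist engagement. So it goes too far to say that leakage would leave no trace. Neither measures expected benefit or disclosure of the hypotheses.

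**Conclusion.** The point holds for the text as written. Section 5.5 gives the hypotheses to the therapists of both arms, while the blinding of participants, and so of both primary outcomes, depends on participants not learning them. No instruction against disclosure is stated. The route is avoidable and runs in the direction of the hypothesis.

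The size of any bias is unknown. The ranges of about 13-70% for pain and 8-37% for function rest on assumed shifts of 0.25 to 0.75 units and 1 to 3 points, no true effect, 83 analysed per group and two-sided 5% testing of each outcome. They show how sensitive the trial is to such a shift, and they do not forecast one.

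A reader might conclude that participant blinding is broken or the primary results invalid. The protocol does not support that: it shows a route, not that participants will learn the hypotheses, and a protocolised intervention offers partial protection. The sample size and the planned analysis are unaffected.

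**What to change.** Replace the last sentence of section 5.5 with: *Physiotherapists will know each participant's programme but will not be told the study hypotheses.* If the present sentence is a slip, this is likely to be close to the intended design.

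Add to sections 5.5 and 8 an instruction to all therapists, including any already aware, not to discuss the hypotheses, the other programme or expected superiority with participants. Use neutral wording about the two programmes in the training session and manuals.

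If therapists do know the hypotheses, say so and qualify the assessor-blinded label for the two primary outcomes.

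The cost is a sentence, an instruction and some editing of training materials. The limits are that some therapists will infer the hypothesis from the add-on design, and any already informed cannot be un-told.

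Repeating the expectation item at 6 weeks is optional. By then expectation would partly reflect benefit already felt, so a difference between arms could not separate leakage from a real early effect.

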### **5.6 Participant Withdrawal**

As participation in this study is voluntary, participants may withdraw from i) participating in either exercise program; and/or ii) continuing with scheduled data collection processes, at any point over their 9-month involvement. Participants may choose to stop attending physiotherapy sessions and/or exercising but continue with some/all aspects of data collection. To minimise data loss, research staff will encourage participants to complete primary outcome measures (at a minimum) at the 3-month time frame, over the telephone if necessary. If a participant withdraws from the study, the nature, timing of and reasons for withdrawal will be recorded (provided the participant responds to contact made by the research team). Any data provided up to the point of withdrawal will be kept in accordance with intention-to-treat analyses, unless the participant specifically requests to withdraw all of their data from the study.

### **5.7 Trial Closure**

For each participant, the follow-up duration is 9 months from randomisation. At this point, final assessment will take place and no further data collection or monitoring will occur for that participant.

### **5.8 Continuation of therapy**

As participants will keep their equipment (e.g. ankle cuff weight, resistance bands) after their involvement in the study has ended, they may choose whether they wish to continue exercising, or not.

## 6. STUDY VISITS AND PROCEDURES SCHEDULE

Study Flow Chart

[figure not shown]

## 7. CLINICAL AND LABORATORY ASSESSMENTS

Figure 1 outlines clinical and laboratory assessment schedule. Only when permitted by the University of Melbourne (i.e. due to COVID-19) will any face-to-face assessments be scheduled for participants. Following enrolment the Trial Coordinator will i) schedule a testing appointment at the University of Melbourne; ii) schedule a cardiorespiratory fitness and body composition appointment at the Be Active Sleep and Eat (BASE) Facility at Monash University; iii) provide a referral and schedule a x-ray appointment [available sites include: Blackburn South Radiology; Bridge Road Imaging; Brunswick Diagnostic Radiology; Healthscan Specialist Imaging Narre Warren; Healthscan Specialist Imaging Ringwood], and; iv) provide a referral for blood collection [all 298 Melbourne Pathology Clinics are available to participants]. The Trial Coordinator will also schedule the first physiotherapy appointment via Zoom. The Trial Coordinator will provide materials (Participant Zoom Information Booklet) to prepare participants to use Zoom prior to their first consultation. At 3-months, participants will be asked to complete the questionnaire booklet online. If participants completed face-to-face assessment at baseline, and if face-to-face appointments are permitted, participants will also be asked to return to i) the University of Melbourne, ii) Monash University and ii) Melbourne Pathology at 3-months. At 9-months, participants will only be asked to complete questionnaires online or hard copy if they prefer. Please note that participants will be asked to opt-in for blood sample assessment at baseline and 3-month follow-up.

### ***X-rays (see Section 4.6)***

If a participant has not had an anteroposterior x-ray of their hip in the past 12 months, they will be asked to attend one of the participating radiology clinics in Melbourne to undergo a standardised anteroposterior (AP) supine hip x-ray. Participants who have undergone a weightbearing or supine anteroposterior or posteroanterior x-ray in the previous 12 months and can provide the images to research staff for screening, will not undergo new x-rays due to ethical concerns of exposing them to unnecessary radiation. Participants who have their own recent suitable hip x-ray will be provided a stamped return envelope to post the x-rays to the research team.

### ***Patient-reported outcomes (see Section 4.6)***

At baseline, participant-reported outcomes will be collected electronically in REDCap via computer or on paper via post (if preferred). At 3- and 9-month follow-up, participants will be sent questionnaires electronically (or on paper if preferred) to complete primary and secondary self-reported outcomes at home.

